### **17. Data Management and Confidentiality**

Given our proposed sample size of 20 participants, we have at least 80% power to detect a 0.53 standard deviation change from baseline to 3 months on a given outcome measure using a two-sided paired t-test with an  $\alpha = 0.05$ . We will report descriptive statistics for the EMA assessments. Paired t-tests (or if data are not normally distributed, the Wilcoxon signed-rank test) will be used to compare the baseline and monthly survey data for the continuous scales. Results will be presented as difference in means or medians with associated 95% confidence intervals. McNemar's test for correlated proportions will be used to compare binary outcomes including the baseline and monthly follow up survey data. Effect sizes will be calculated for all measures to further quantify the degree of efficacy. A recruitment rate of 30% and retention rate of 80% would indicate feasibility for a larger trial. Statistical analysis will be conducted using SAS v. 9.4 (Cary, NC) and significance will be assessed at the 0.05 level.

All questionnaire data will be collected using REDCap software. Data related to wearable devices will be collected using the manufacturer's software. To maintain participant confidentiality, all participants will be assigned a study identification number. The codes

[figure not shown]

that link the name of the participant and the study identification number will be kept confidential by the PI in a secured cabinet.

Upon data storage, all data will be de-identified. Only the authorized study team on this proposal will have access to the data. All study staff will complete biomedical or socio-behavioral training through the Collaborative IRB Training Initiative Program (CITI). We will store the data on the Emory server. The server is protected by the Emory network, and a secured log-in is required from all users. Data will be stored only until final analysis and publication of any manuscripts, after which the data files will be removed. No data will be released to other agencies.

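### In the signed-rank branch, the reported difference in medians, read as written, is not the quantity the test addresses, so estimate and interval fit the p-value poorly

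*Protocol*

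**What the plan says.** Section 17 of the protocol (Data Management and Confidentiality) fixes the test for the continuous survey scales: "Paired t-tests (or if data are not normally distributed, the Wilcoxon signed-rank test) will be used to compare the baseline and monthly survey data". The next sentence fixes what is reported: "Results will be presented as difference in means or medians with associated 95% confidence intervals". For the analyses, "significance will be assessed at the 0.05 level".

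The section does not mention the median of the within-person differences or a Hodges-Lehmann estimate, and does not say how an interval for medians would be built. The sample size is 20. The feasibility criterion includes 80% retention: "A recruitment rate of 30% and retention rate of 80% would indicate feasibility for a larger trial". Section 2 says that the pilot data will support a funding application for a larger cohort. Section 4 makes recruitment, retention and usability the primary endpoints.

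**The concern.** The difference between two means equals the mean of the paired differences, so the t-test branch tests and reports the same thing. Medians have no such identity. The follow-up median minus the baseline median compares two marginal distributions, while the signed-rank test looks at the centre (pseudo-median) of each participant's change. In the non-normal branch the protocol would therefore test one quantity and report another.

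Two consequences follow. A significant p-value can stand beside an interval that includes zero, and the interval gives up part of the precision gained by measuring the same adolescents twice. In a pilot, the estimates and intervals are what pass into the planning of the next study. Short questionnaire scores in at most 20 participants make the non-normal branch a realistic path, although the protocol gives no score distributions to show how often it would be used.

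**Working it through.** **Inputs from the protocol (Section 17).** 20 pairs; 80% retention, so 0.80 × 20 = 16 pairs; signed-rank test; significance level 0.05; 95% intervals.

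**Inputs assumed, because the protocol gives none.** Integer scale 4-20, right-skewed, SD about 4; within-person correlation 0.5-0.8; true shift 0.3-0.5 SD; percentile bootstrap of pairs for the difference in medians.

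**The plan's own figure.** The protocol gives no figure on this point. The section's one power statement ("we have at least 80% power to detect a 0.53 standard deviation change from baseline to 3 months") concerns the paired t-test. With 20 pairs the noncentrality is 0.53 × √20 = 2.37 on 19 df, and two-sided power at 0.05 is 61.4%, not 80%. It reaches 80% only if 0.53 is in raw-score SDs and the within-person correlation is about 0.68. That is a separate matter, and nothing below uses it.

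**Step 1: a 20-pair example that can be checked by hand.** Baseline: 4, 5, 6, 7, 8, 8, 9, 9, 10, 10, 10, 10, 11, 11, 12, 13, 14, 15, 16, 17. The six lowest and six highest scorers each rise by 2; the other eight do not change.

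- The 10th and 11th ordered values are 10 and 10 at both times, so the difference in medians is 10 − 10 = 0.
- The paired differences are eight zeros and twelve 2s, so their median is 2.
- Signed-rank test: all 12 non-zero differences are positive. Exact p = 2 × (1/2)^12 = 0.00049; normal approximation 0.00053.
- Hodges-Lehmann estimate: the median of the 20 × 21/2 = 210 pairwise averages. These are 8 × 9/2 = 36 zeros, 8 × 12 = 96 ones and 12 × 13/2 = 78 twos. The 105th and 106th values are both 1, so the estimate is 1.
- The interval takes the 53rd value from each end, giving 1 to 2.

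The same data give p = 0.0005, a difference in medians of 0, a median paired change of 2 and a pseudo-median of 1. These are three different estimands, and only the last belongs to the test.

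**Step 2: size on integer scales (simulation under the assumptions above).**

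| | Difference in medians | Hodges-Lehmann |
|---|---|---|
| Interval width, relative | about 1.3-1.7 | 1 |
| Interval includes zero when signed-rank p<0.05 | roughly 55-80% | about 10-35% |

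If width goes as 1/√n, ratios of 1.3 and 1.7 match a Hodges-Lehmann interval from 1/1.3² = 59% and 1/1.7² = 35% of the pairs.

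**Step 3: size on continuous scores without ties (n = 20).** The variance of the difference in medians, relative to that of the Hodges-Lehmann estimate, is 1.8, 2.2 and 3.3 at correlation 0.5, 0.7 and 0.9 (normal margins; gamma margins are similar). With a true change of 0.66 SD of the differences, the signed-rank test and the pair-bootstrap interval disagreed in about 29%, 37% and 51% of simulated trials. The Hodges-Lehmann interval disagreed with the exact test in 0%.

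**Step 4: how often the extreme case occurs.** A significant test beside a zero or opposite-sign difference in medians occurred in 0.1-2.5% of datasets on continuous scores and in 0.6-2.4% on rounded ones. The usual conflict is a small p-value beside a wide interval that includes zero.

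**Step 5: the other reading.** If the median of the paired differences is meant, its SD relative to Hodges-Lehmann under gamma margins is 0.301/0.291 = 1.03, 0.233/0.229 = 1.02 and 0.131/0.131 = 1.00 at correlation 0.5, 0.7 and 0.9. Under normal margins it is 0.270/0.230 = 1.17 at correlation 0.5. With skewed scores, where this branch applies, the width loss is essentially gone.

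**The case against.** The strongest reply is that the phrase is shorthand. It directly follows two tests that are both computed on within-person differences, so it may mean the mean or median paired difference. The protocol never spells out a subtraction of one median from another. This is a fair reading, and under it most of the problem goes. What stands is that someone who subtracts the two medians also complies with the text, and that even the median paired difference is not quite what the test addresses (2 against 1 in the example).

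A second reply is that the interval method is unstated and commonly left to an SAP. That also stands in part: the width figures rest on a bootstrap chosen here. The choice of reported estimate, however, is in the protocol.

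A reader might infer that the plan throws away the pairing. The documents do not support that. With the pairs kept, correlation of 0.5 to 0.9 still cuts the variance of the difference in medians by 36-76% (50-90% for Hodges-Lehmann). The whole gain would go only with an unpaired interval, which the protocol does not specify. A reader might also infer that zero or reversed effects beside significant tests would be common; Step 4 shows that they would be rare.

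Finally, the reach is limited. The feasibility criteria do not use this estimate, and Section 17 also promises effect sizes for all measures.

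**Conclusion.** The point holds in limited form. Read as written, the protocol reports a quantity in the signed-rank branch that the signed-rank test does not address. The cost is an interval about 1.3-1.7 times too wide that often includes zero beside a significant test. These sizes depend on the assumed score distribution, correlation, shift and bootstrap interval, none of which the protocol states. If the median paired difference was intended, what remains is an ambiguity and a small mismatch. The issue is confined to the non-normal fallback for the baseline-to-monthly survey comparisons; the t-test branch and the feasibility endpoints are untouched. It is worth correcting because the correction is nearly free, not because it threatens the study's primary conclusions.

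**What to change.** Replace the reporting sentence in Section 17 with wording such as:

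> For each continuous scale we will report the mean of the within-person differences with its t-based 95% confidence interval or, where the signed-rank test is used, the Hodges-Lehmann estimate (pseudo-median) of the within-person differences with the 95% confidence interval obtained by inverting the signed-rank test. Baseline and follow-up medians will be shown descriptively only.

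The text should say pseudo-median rather than median paired difference, because the two differ when the differences are asymmetric.

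The cost is one sentence and a few lines of SAS code, with no extra data or participants. The Hodges-Lehmann estimate is less familiar to readers, and with ties or zero changes its interval will not agree with the test in every dataset.

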#### **18. Provisions to Monitor the Data to Ensure the Safety of Participants**

We will establish a Data and Safety Monitoring Plan that consists of the PI and co-investigators. In order to ensure the integrity and validity of the data, [name] will conduct a routinely review of reports that describe study operations and present data to ensure that problems are identified and corrected in a timely manner. The following reports will be generated for routine review:

- Screening, recruitment, enrollment, and retention reports
- Protocol compliance reports to identify protocol deviations
- Data quality reports – describe missing, erroneous, and inconsistent data to ensure protocol is followed and deviations are tracked
- Identification/reporting of serious adverse events

If data quality and integrity issues are uncovered, the following correction processes will occur:

- If the quality of the data compromised, an audit of all related data will be conducted by [name].
- If systematic errors are uncovered, [name] will review these errors and update the protocol (with IRB approval) to address the cause of the systematic errors.
- If detection processes are not adequately discovering issues related to data quality, new processes will be developed to adequately detect data quality issues.
- If systematic protocol violations are occurring, staff will be retrained by [name].

Diligent safety monitoring will be conducted throughout this study in compliance with the following required elements of the Emory IRB's continuing review process:

1. tracking of subject accrual (enrollment, drop-outs, demographics)
2. timely and appropriate reporting of informed consent process deficiencies, protocol deviations, privacy breaches, conflicts of interest, and/or changes in personnel
3. ongoing monitoring and appropriate reporting of adverse event activity including:

[figure not shown]

- a. frequency of unanticipated, internal, related or possibly related, and serious or more prevalent than expected adverse events
  - b. frequency of deaths occurring during the study or within 30 days of study termination, even if expected or unrelated
4. interim assessment of risk/benefit relationship in reference to adverse event occurrences, preliminary observations, and emerging information
5. timely and appropriate IRB submission of safety-related documents such as audit reports, sponsor progress reports, and other materials or communications that might impact the safe conduct of this study
6. active cooperation with the IRB and other applicable entities in the event of a random or for-cause internal or external audit

The PI and co-investigators will meet monthly to review data quality and safety events, including any protocol deviations, and to adjudicate adverse events. Additionally, participant safety monitoring will occur at each follow-up study visit.

### **19. Provisions to Protect the Privacy Interests of Participants**

Participants will interact with the research coordinator during both the informed consent process and in data collection. Both of these tasks will be carried out in a private research room. There will be no other individuals interacting with or observing the participants.

The PI, who may be familiar with participants from their time receiving treatment in the clinic, will also interact with participants to answer study-related questions as needed. All questions will be answered in a private setting in order to reduce the risk of observation by anyone not participating in the research.

Only the PI and research coordinator will be able to access the participants' medical for the sole purpose of determining eligibility. Only the authorized study team on this proposal will have access to study-related data. All study staff will complete biomedical or socio-behavioral training through the Collaborative IRB Training Initiative Program (CITI). Data will be stored on the Emory servers in password-protected files.

### **20. Economic Burden to Participants**

Individuals will not incur any medical costs by participating in the proposed study. Participants will be provided with all study devices. Participants will need to have their own smartphone with data plan to participate; participants will be provided \$25 in the form of a gift card to offset additional data usage when completing the EMA, in addition to the compensation for study completion as outlined in Section 13.

### **21. Consent Process**

Written informed consent or electronic consent with legal e-signature (for telemedicine/virtual enrollment) will be obtained for all individuals on the same day as initial data collection. Electronic consent/assent will be obtained via REDCap, which will allow to study team to obtain a legally binding electronic signature. Individuals who are 18 years old will provide written/electronic consent themselves. For individuals younger

[figure not shown]

than 18 years, parental permission will be provided by the parent or legal guardian. In addition, written/electronic assent will be obtained for all individuals under 18 years. For individuals presenting in-person, eligible patients will be approached by the research coordinator in the waiting room of the CHOA Adolescent Medicine Practice. Patients will be asked if they are interested in learning more about the study. If so, the eligible patient will be led by the research coordinator to the research room of the CHOA Adolescent Medicine practice, which is a private office within the clinic. The research coordinator will then carry out the consent/assent process with the patient and his/her parent or legal guardian. For individuals presenting via telemedicine/virtually, they will be asked by their physician if they are interested in learning about the study. If so, they will be informed that they will receive a follow-up call by the research coordinator to schedule a time to discuss the study via Zoom. During the scheduled Zoom videoconference, the research coordinator will carry out the consent/assent process with the patient and his/her parent or legal guardian. The consent process will take approximately 15 minutes. If the eligible participant or the parent/legal guardian has any questions about the study, they will be answered at this time. In order to minimize the possibility of coercion or undue influence, the consent process will be carried out by the research coordinator, who has no influence on or connection to the medical care received by the patients. The research coordinator will not obtain a signature for consent until the entire study has been explained and all questions have been answered.

#### **Non-English-Speaking Participants**

The data collection instruments used in the study will be written in English. Therefore, it will be inappropriate to include subjects who are not proficient in English in this pilot study. This is not to say that the research topic does not apply to adolescents who are not proficient in English; however addressing these populations within the proposed pilot study would not be possible.

#### **Participants who are not yet adults (infants, children, teenagers)**

Prospective participants who have not attained the legal age for consent (e.g. individuals under the age of 18 years), as determined by the age in their medical record, will be required to give written/electronic assent. Written/electronic parental permission will also be obtained for these individuals. Parental permission will be obtained from one parent, even if the other parent is alive, known, competent, reasonably available, and shares legal responsibility for the care and custody of the child. Only parents or legal guardians listed in the child's medical record will be able to provide permission.

## **22. Setting**

The research team will recruit 20 patients at the Children's Healthcare of Atlanta (CHOA) Hughes Spalding Adolescent Medicine practice. Patients will be screened for eligibility at the time of their visit. Eligible teens presenting to the clinic in-person will be approached by the research coordinator in the waiting room to see if they would be interested in

[figure not shown]

learning more about the study. If so, the research coordinator will lead the patient to a private research room in order to provide an overview of the study, carry out the consent/assent process as described in Section 21, and carry out all study procedures. Alternatively, participants will have the option to complete the study enrollment and consent/assent virtually with legal e-signature via REDCap if they prefer to leave the clinical environment after their appointment. Teens presenting via telemedicine will be asked by their physician if they are interested in learning about the study. If so, they will be informed that they will receive a follow-up call by the research coordinator to schedule a time to discuss the study via Zoom. During the scheduled Zoom videoconference, the research coordinator will explain the study in detail, carry out the consent/assent process as described in Section 21, and carry out all study procedures.

### **23. Resources Available**

The CHOA Hughes Spalding Adolescent Medicine Practice serves approximately 2000 adolescents ages 13-21 years of age annually for primary care wellness visits, as well as consultative behavioral/mental health and reproductive health visits. For the proposed study, we will need to recruit 20 participants ages 13-18 years in a two-month time span. The Adolescent Medicine Practice sees patients three days out of the week. We will devote each of those three days to recruitment in order to reach our recruitment goal.

Both medical and psychological resources are available to participants who experience anticipated consequences of human research. [name], the project PI, is a provider at the CHOA Adolescent Medicine practice and is able to provide research-related care to patients as needed. The Adolescent Medicine practice also has two additional medical doctors, a nurse practitioner, and a licensed psychologist who will be made aware of the research study and will be able to provide care as needed to patients experiencing any stress identified via the research protocol.

All persons assisting with the research will be adequately informed about the protocol, research procedures, and their duties and functions. Furthermore, all persons assisting with the research will receive appropriate CITI training for human subjects' research.

